**Fig. 2 Fig2:**
[figure not shown]
CONSORT flow diagram, estimations on eligibility are based on data of 2020, T0 data from October 2020 to September 2022 is analyzed retrospectively. Source: http://www.consort-statement.org/, Version of 2010 (12.11.2021)

### Data collection, completeness, and quality

The data used for the study include all antibiotic prescriptions for patients with statutory health insurance (SHI) that were filed at a pharmacy. In addition, the outpatient claims data of the participating SHI funds (according to §295 SGB V) are used for the diagnosis information of the included patients. Thus, the trial is based on pseudonymized routine data based on GP level. Information collected includes age groups and sex of patients, ARTI diagnoses (grouped and individual diagnoses), antibiotic prescriptions, group affiliation of the physician (intervention vs control), region, and level of urbanization. Thus, a fairly complete data set is available on each GP and the patients treated in the respective practice. However, since the data are not collected for scientific reasons, there are some relevant limitations: The information on the diagnosis depicts the coded morbidity according to ICD10-GM. In particular, the severity of the disease or the patient’s condition may not be adequately reflected by the coded diagnosis. Moreover, there is no connection between diagnosis and prescription in our data. Therefore, we have developed an algorithm that allows a reliable association between diagnosis and prescription. First, different inclusion and exclusion diseases are defined based on ICD-10 diagnosis codes. A patient may not have received both an inclusion and an exclusion diagnosis within a quarter. Furthermore, only one disease group (e.g., upper respiratory tract infections) may have been coded within a quarter. In order to exclude misclassifications of initial prescriptions due to severe courses, patients diagnosed by physicians of different specialties are excluded. To ensure the most accurate assignment of diagnoses and prescriptions, the diagnosing practice must also be the prescribing practice. This rule is only deviated if the pseudonym of the prescribing practice has not billed any case in the entire calendar year. In this case, an error in the pseudonymization is to be assumed and the prescription is automatically attributed to the diagnosing practice. However, we still do not know whether the prescription was only filed or actually taken by the patient. This could lead to a slight overestimation of the actual antibiotic consumption among patients in outpatient care.

### Statistical methods

All prescription rates for the primary and secondary outcomes are presented descriptively for the entire sample and separately according to groups. Sampling units are practices. A negative binomial regression model will be used to evaluate whether the change of prescription rates differs between control and intervention(s) (primary outcome). The negative binomial model is used because we assume that the mean and variance for prescription rates will be different (also seen in the RESIST study). Hereby, the number of antibiotic prescriptions after the intervention(s) is considered as the dependent variable, the number of patients is treated as the offset variable, the grouping variable and the area of the respective regional ASHIP are fixed effects, and the rate before the introduction of the intervention(s) is a covariate in the model. Although we used the Bonferroni-corrected significance level within the sample size calculation, we will evaluate the primary outcome with the less conservative Dunnett test which uses the information that the three interventions will be compared to the same control. The resulting adjusted *p* values will be compared to the global significance level of 5%.

The secondary outcomes will be exploratively analyzed using a negative binomial model without adjustment for multiple testing. Thereby, the dependent variables are the prescription rates for cephalosporins and fluoroquinolones, respectively. The fixed effects are the grouping variable, the area of the respective regional ASHIP, and the rate before the introduction of the intervention(s) for cephalosporins and fluoroquinolones, respectively. The number of patients serves as the offset variable.

The ITT population will be primarily used for all analyses. Thereby, we can answer the question about the effect of offering online training or peer-moderated online training. In a further explorative analysis, the comparisons are repeated in the PP population to examine the effects according to the training received. This population includes all practices in which the GPs participated in the training offered. Only the result of the primary analysis in the ITT population will be interpreted in a confirmatory sense. The results will be reported according to the CONSORT statement [26]. Incidence rates, rate ratios, associated 95% confidence intervals, and *p* values will be reported. The analysis is done with standard statistical packages such as SAS, Stata, R, or SPSS [27–30]. In addition, explorative subgroup analyses will be conducted in both the ITT population and the PP population, relating to the effect of the intervention on prescription rates or drug selection for individual indications (respiratory tract infections, urinary tract infections). In an extended multivariable analysis, reasons for an indicated prescription are also taken into account as well as patients’ multimorbidity, failure of previous therapy, or the size of the practice. If the number of cases is large enough, regionalized analyses will also be performed.

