### Interventions

We test three interventions against the control group: (A) personalized feedback on own prescribing behavior in comparison to GPs of the region within a visual attention-grabbing graph (social norm feedback), (B) feedback like (A) plus an invitation to participate in the project’s own online training (eLearning) on rational prescribing practice and communication strategies, and (C) feedback like (A) plus an invitation to participate in an online peer-moderated training in quality circle format on the topic of rational antibiotic prescribing, communication strategies, and development of individual starting points for a sustainable behavior change. In detail, the interventions are designed as follows:*Group A* receives personalized, individual prescription feedback, which compares the GP’s prescription behavior relative to colleagues in the region. This is complemented by a simple but appealing graph of one’s own prescription quantity compared to the average prescription rate of peers in their region (social norm feedback). This shall encourage to critically question one’s own prescribing behavior.*Group B* receives personalized, individual prescription feedback as in (A), and in addition, an invitation to participate in a project-specific online training. The online training fulfills two requirements that initially seem contradictory. It must be generalizable and thus ensure broad application. At the same time, it must address the various causes of inadequate prescription practice. It is also known that for the group of high prescribers a “one fits all” approach cannot be effective since according to Rodgers they belong predominantly to the group of “late adopters” [14]. This apparent paradox for the design of the online training is resolved by a modularized intervention concept. The aim is to provide an individualized portfolio of relevant training modules for each participant in an automated way, which addresses, among other things, the main phenomena of non-rational prescription of antibiotics described in the literature. These include (a) dealing with unavoidable diagnostic uncertainty [15], (b) the mostly unfounded fear of making mistakes, (c) perceived prescribing pressure from patients [16, 17], (d) basic clinical misconceptions [18], (e) the use of treatment algorithms inappropriate to the setting (e.g., treatment regimens of hospital care applied to primary care), and (f) rational consideration of practice characteristics, such as a high proportion of particularly vulnerable patient groups (e.g., due to demographic characteristics, a high proportion of inpatient care facilities, or deprived population groups) [15]. Participating GPs undergo an initial assessment at the beginning of the online training. This assessment captures GPs’ attitudes and individual awareness of the problem of inappropriate antibiotic prescriptions. A pre-developed, weighted algorithm considers the respective information provided by the training participants and proposes an individually tailored module portfolio. For optimally addressing participants, the Transtheoretical Model of Behaviour Change (TTM) by Prochaska and Di Clemente is taken into account [19]. The TTM describes several stages on the way to a change in behavior. It originates from behavioral psychology and is used in interventions to change health behaviors, e.g., tobacco smoking and alcohol consumption, but also in changing medical (prescribing) behavior [20, 21]. The content of the modules focuses on knowledge transfer (e.g., guideline update, antibiotic substances), problem-solving strategies (e.g., doctor-patient communication, intercultural communication, safety netting), everyday strategies (e.g., medical documentation, integration of point-of-care tests, and delayed prescribing) and content that encourages reflection (e.g., evidence-based medicine, medical ethics). Depending on personal interest and recommended modules, the duration of the online training is estimated to range between 90 and 180 min (45 min minimum). If interested, participants can ask for information material to be sent to them afterwards.*Group C* receives personalized, individual prescription social norm feedback like (A), and in addition, the invitation to participate in a peer-moderated online training similar to quality circles. These peer-moderated trainings are each moderated by a GP colleague (peer), who already has experience in moderating quality circles. To prepare for the peer intervention, the peers undergo a specific online training. In the first part of the training, peers participate in online training on the intervention (B). In the second part, the peers are trained in three areas according to current medical-didactic findings [22, 23]: giving constructive feedback, motivational interviewing [24], and dealing with group dynamics in heterogeneous groups. The latter is also relevant regarding “difficult participants” in order to recognize and address resistance within the group. The trained peers then moderate the exchange with the participants in an online training and provide content of the individual modules according to their needs. Here, too, change management is to be initiated using TTM. For this purpose, the peer discusses value concepts as well as the individual problem awareness for inadequate antibiotic prescriptions within the group at the beginning of the event. The peer can thus focus and reflect on the intervention content according to the group specifics, both on the cognitive level and on the behavioral level.

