### Sample size

We assume that a total antibiotic prescription rate of 12% (rate of high prescribers in the predecessor project RESIST, unpublished data) will be observed in the control group. This rate is expected to be reduced to 8.7% in group A, to 8% in group B, and to 7% in group C. Since all interventions shall be compared to the control, we adjust for multiple testing via the Bonferroni correction and hence the type 1 error is set to 1.67% (two-sided). A Poisson model was used for sample size calculation. To be able to show the effect assumed for the comparison between the control group and group A with a power of 80%, 2000 practices are required in both groups. Due to the feasibility, maximal 1250 practices can be included in group C for comparison to the control. Thereby a power of 98.8% can be gained. Group B consists of 2000 practices to include all remaining eligible practices in all nine participating regional ASHIP. For the comparison between the control group and group B, a power of 94.6% can be gained. This sample size calculation refers to the intention-to-treat (ITT) population. This population includes all randomized practices regardless of whether they accept the offer of training in groups B and C. However, we are also interested in the per-protocol (PP) population which is analyzed within a secondary analysis. The PP population includes only those practices in groups B and C that participated in the training courses according to protocol. Thus, only the assumed effects between the control group and groups B and C change. We assume that in group B, the rate in this population can be reduced to 7.5%. Furthermore, we assume a participation rate between 30% and 40%, i.e., between 580 and 800 practices participate in the online training. Assuming this difference and the Bonferroni adjusted type 1 error of 1.67 a power between 80% and 89% can be gained. In group C, we assume a participation rate between 17% and 20%, i.e., between 215 and 250 physicians will presumably participate in the peer-moderated online training. Under the assumption of a reduction to 6% and the Bonferroni adjusted type 1 error of 1.67 a power between 80% and 85.8% can be gained See Fig. 2.

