### Risk of bias

There are several risk factors that could influence the success of the project: It is possible that there is too little acceptance on the part of the GPs contacted, resulting in low-participation rates in the interventions offered. In the case of peer-moderated training, this could lead to heterogeneous group sizes and the desired intercollegiate exchange not being able to take place due to a low number of participants. To counteract this, a sufficiently high number of GPs is contacted, and the content of the letters is closely coordinated with the regional ASHIP experienced in this field. Participation is also incentivized by an expense allowance. In addition, the training courses are conducted online in a format similar to quality circles to maximize acceptance among GPs. Another external risk factor that cannot be influenced is a higher or lower level of disease activity in the period under review (wave of flu, Sars-CoV-2 pandemic, other disruptive effects, or overlapping events) than in the preintervention period used for the evaluation. As a countermeasure, in addition to a pre-post comparison with an extended comparison period, a comparison to non-contacted high prescribers in the participating regions (Group D as a “real control group”) is also carried out here.

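### Group C practices are trained together under a shared moderator, but the per-protocol model treats them as independent, so with any positive within-group correlation the exploratory group C intervals and p values are too optimistic

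*Protocol article*

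**What the plan says.** **Delivery (Interventions).** Group C is offered online training in quality-circle format. Each training is moderated by one GP peer, who opens with a group discussion and shapes the content to that group: "The peer can thus focus and reflect on the intervention content according to the group specifics, both on the cognitive level and on the behavioral" […]. Group A receives a letter, group B a letter plus individual online training, and the control group is not contacted. Only group C therefore has training groups.

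**Group size (Risk of bias).** No number is given. The article warns that, if few GPs take part, "this could lead to heterogeneous group sizes and the desired intercollegiate exchange not being able to take place due to a low number of participants". Exchange between participants is thus part of what the intervention is meant to do.

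**Analysis (Statistical methods).** "Sampling units are practices. A negative binomial regression model will be used to evaluate whether the change of prescription rates differs" […]; the contrast is each intervention against control. Arm and regional association are fixed effects, the baseline rate is a covariate and the number of patients is the offset. There is no term for training group or moderator. For the exploratory analysis, "the comparisons are repeated in the PP population to examine the effects according to the training received". Rate ratios, 95% confidence intervals and p values are to be reported. Only the ITT result is confirmatory.

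**Power (Sample size).** The article expects that "between 215 and 250 physicians will presumably participate in the peer-moderated online training". From this number and an assumed effect it derives the PP power: "Under the assumption of a reduction to 6% and the Bonferroni adjusted type 1 error of 1.67 a power between 80% and 85.8% can be" […]. No design effect, group size or ICC is mentioned.

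**The concern.** Practices that share a session, a moderator and group-specific content may change their prescribing in similar ways. This grouping exists in one arm only, which makes the design partially nested. The negative binomial dispersion parameter allows extra variance for each practice, but it does not model covariance between practices. The region term does not replace a group term, because nine regions cannot identify individual training groups.

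In the PP population every group C practice belongs to a training group, so the problem applies in full there. At stake is the precision reported for the comparison that is meant to show what the training itself does. A difference due to a few good or poor moderators could be read as an effect of peer training. The group C interval would also look more precise relative to group B than it is, and the Discussion wants to set the individual format against the peer format.

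**Working it through.** **Inputs from the Sample size section.** Control rate: "We assume that a total antibiotic prescription rate of 12"%. Group C PP rate 6%, ITT rate 7%. Control n = 2000, group C ITT n = 1250, group C PP n = 215 to 250. Alpha: "the type 1 error is set to 1.67% (two-sided"), so z = 2.394.

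**Inputs assumed.** Practices per training group m = 5 to 15, middle value 8. ICC = 0.01 to 0.10, middle value 0.05. Neither is in the article.

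**Step 1: reproduce the plan's power.** An unpooled Poisson rate difference with one exposure unit per practice:

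power = Φ[(r1 − r2)/√(r1/n1 + r2/n2) − 2.394]

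- n = 215: 0.06/√(0.12/2000 + 0.06/215) = 3.258; Φ(0.864) = 80.6% (stated 80%).
- n = 250: 0.06/√(0.12/2000 + 0.06/250) = 3.464; Φ(1.070) = 85.8% (stated 85.8%).

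The same formula gives the other stated figures: A 80.2%, B 94.6%, C ITT 98.8%, B PP 81.0% (n = 580) and 89.2% (n = 800). The stated powers therefore count all practices as independent.

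**Step 2: design effect.** DE = 1 + (m − 1) × ICC.

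- m = 5, ICC 0.01: 1.04
- m = 8, ICC 0.05: 1.35
- m = 15, ICC 0.10: 2.40

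**Step 3: standard error and error rate of the PP comparison.** With equal variance per practice in both arms, group C contributes the share s = (1/n_C)/(1/n_C + 1/2000) of the variance. At n_C = 232, about the middle of 215 to 250, s = 0.896.

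True SE / model SE = √(1 − s + s × DE)

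Actual error at nominal 5% = 2[1 − Φ(1.96/SE ratio)]

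| m | ICC | DE | SE ratio | actual error |
|---|---|---|---|---|
| 5 | 0.01 | 1.04 | 1.02 | 5.4% |
| 8 | 0.05 | 1.35 | 1.15 | 8.7% |
| 15 | 0.10 | 2.40 | 1.50 | 19.2% |

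A simulation of the negative binomial model gave rejection rates of 5.2% (m = 8, ICC 0), 9.8% (8, 0.05), 12.6% (8, 0.10) and 12.5% (12, 0.05). It used 1500 runs, 2000 control and 232 group C practices, about 1000 patients per practice, a 12% rate and a residual log-SD of 0.25. The practice numbers in these settings other than the 2000 controls, the patient count and the log-SD are assumptions.

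**Step 4: the ITT comparison.** At most about 20% of group C attends, so DE = 1 + 0.2(m − 1) × ICC, with n_C = 1250 and s = 0.0008/0.0013 = 0.615. DE is 1.008, 1.07 and 1.28 in the three scenarios, and the actual error is 5.1%, 5.5% and 7.0%. ITT power on the plan's formula stays between 97.5% and 98.7%, against 98.8%.

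**Step 5: what can be said about PP power.** Multiplying the group C term of the plan's formula by DE gives, for n = 215 and 250:

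- DE 1.04: 79.2% and 84.5%
- DE 1.35: 68.3% and 74.8%
- DE 2.40: 43.1% and 49.4%

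These figures are conditional on the formula's variance, which implies a per-practice SD of √0.12 = 0.35 in control and √0.06 = 0.24 in group C. With the simulation's variance instead (1000 patients, log-SD 0.25), n = 215 and DE 2.40, the expected z for 12% versus 6% is ln 2/√[(1/120 + 0.0625)/2000 + 2.4(1/60 + 0.0625)/215] = 22.9, so power is practically 100%. The between-practice variance decides the matter, and the article does not give it.

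**The case against.** **Power.** A reader might infer that the stated 80% to 85.8% is not delivered. The documents do not support that. Step 5 shows that power falls only if the formula's very large per-practice variance is kept. With a common SD of the practice rate of 0.10 or less (assumed), power at n = 215 stays above 99% even at DE 2.4. What stands is narrower: the printed figure assumes no within-group correlation and does not say so.

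**The size is assumed.** Group size and ICC are not in the article, and 5.4% to 19% runs from trivial to serious. The article's worry about low attendance points to small groups and so to the lower end. This is fair, and is why only a range is given.

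**The null is special.** If training changed nothing in any practice, a shared session would create no correlation. The inflated error needs group or moderator effects that differ but average to zero, or sorting into groups beyond region and baseline rate. This is correct for the test. The interval is also too narrow when training works but works unevenly across groups.

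**The analysis is exploratory.** The PP comparison sets volunteers against all controls, so it is not randomised, and no confirmatory claim rests on it. This limits the importance of the point. The intervals and p values will still be reported, however.

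**It could be left to an analysis plan.** The article does not merely omit the matter. It fixes the unit and the model terms and says that the same comparisons are repeated in the PP population.

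**Conclusion.** The point holds for the exploratory group C PP analysis. Applied as written, the model understates that comparison's standard error whenever outcomes within a training group are positively correlated. Under the assumed 5 to 15 practices per group and ICC of 0.01 to 0.10, the understatement is a factor of about 1.02 to 1.5, and a nominal 5% test has an actual error of about 5.4% to 19%. Groups A and B are not affected. The confirmatory ITT test is barely affected (5.1% to 7.0% under the same assumptions), and its model need not change. The article does not allow a conclusion on whether the true PP power is above or below the stated figure. The change is worth making because it is cheap and because group membership may be hard to recover later from pseudonymised data.

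**What to change.** 1. Record a training-group code for each group C participant, or a moderator code if one peer leads several groups. Pass it on with the participation flag that already defines the PP population.
2. In the PP analysis, add a random effect for training group in group C only. Alternatively, use standard errors clustered on training group with a small-sample correction. All other practices count as clusters of one. The correction matters: uncorrected clustered errors still rejected in 6.1% to 8.5% of the simulated runs. The corrected version was not simulated, so it should be checked before it is fixed.
3. Optionally, repeat this as a sensitivity analysis of the ITT comparison of C with control. Leave the primary model as it is.
4. In the Sample size section, state that the 80% to 85.8% for group C assumes no within-group correlation, or give PP power over a range of group size and ICC with the between-practice variance stated.

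Cost: one code per participant and a few lines of analysis wording. No extra practices or outcome data are needed. The downside is a somewhat wider PP interval for group C.

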## Methods

### Trial design

The ElektRA study is a 4-arm cluster-randomized controlled trial addressing high antibiotic prescribers among German GPs of nine regional Associations of Statutory Health Insurance Physicians (ASHIP). On their behalf, the Central Research Institute of Ambulatory Health Care in Germany (Zi) analyses all outpatient claims and prescription data (T0, October 2020–September 2022). Based on this data set, we can identify GPs who use antibiotics or problematic agents (e.g., fluoroquinolones) more frequently than their colleagues. From this pool, GPs are randomized into four groups: a non-contacted control group and three intervention arms (A–C). Within these arms, we test (A) *social norm feedback* on antibiotic prescribing, (B) *social norm feedback* plus *online training* on rational prescribing practice and communication strategies, and (C) *social norm feedback* plus *online peer-moderated training* on rational antibiotic prescribing, communication strategies, and sustainable behavior change. Randomization is stratified by region. GPs in groups A–C will be contacted by their respective regional ASHIP. The primary outcome is the overall rate of antibiotic prescriptions, measured as the proportion of patients with antibiotic prescriptions out of all patients with a prescription. Outcomes are measured over a period of 15 months (T1, October 2022–December 2023) after randomization. In addition, a mixed-method process evaluation is carried out.

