### Participants

The Zi uses a summative score to determine potentially eligible GPs and GP practices based on German prescription and outpatient claims data before intervention (T0, October 2020–September 2022). The maximum score value is six. A GP or GP practice obtains one additional point if its own value in one of the aspects exceeds the 75% percentile of antibiotic prescribing within the respective region. Here, a region represents the area for which a participating ASHIP is responsible. In Germany, there are in total of 17 of those regions, 9 of which are participating in this study. For inclusion, more than two points are necessary. The aspects listed in Table 1 are used for score formation.

**Table 1 Tab1:** Aspects considered for score formation

1	Overall prescription rate (ratio of patients with antibiotic prescriptions to patients with any prescription)
2	Prescription rate for upper respiratory tract infections (ratio of patients with upper respiratory tract infection to antibiotic prescriptions for these patients)
3	Prescription rate for lower respiratory tract infections (ratio of patients with lower respiratory tract infection to antibiotic prescriptions for these patients)
4	Prescription rate of fluoroquinolones (2 points possible): total prescription rate of fluoroquinolones (ratio of patients with fluoroquinolone to patients with antibiotic) and/or fluoroquinolone prescription rate for urinary tract infection (ratio of urinary tract infection patients with fluoroquinolone to urinary tract infection patients with antibiotics)
5	Prescription rate of cephalosporins (ratio of patients with cephalosporin to patients with antibiotics)

After identification, the GPs or GP practices meeting the inclusion criteria are randomized and stratified by region. As identification is based on pseudonymized data, an independent trust center will generate study pseudonyms that will enable all participating regional ASHIP and the Zi to communicate about identified entities and allow the ASHIP to re-identify these eligible GPs or GP practices and contact them. The Zi on the other hand will always exclusively work with pseudonymized data to compile all further analyses, e.g., those necessary for providing GP-specific prescription feedback. Physicians who have already participated in the RESIST Innovation Fund project [13] are excluded because they have already received e-learning on optimizing antibiotic prescribing.

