### Outcomes

The primary outcome is the overall rate of antibiotic prescriptions, measured as the proportion of patients with antibiotic prescriptions out of all patients with prescriptions within the nine regional ASHIPs before intervention (October 2020–September 2022) and after it officially starts (October 2022–December 2023). All interventions are completed by December 2022. The changes in prescription rates between those two-time frames are compared between the control group and the interventions. Effects measured at this level are very robust, as neither imprecision in diagnosis coding (ICD 10) nor possible changes in coding behavior have an influence on this outcome. The same applies to the secondary outcomes. Secondary outcomes are the overall prescription rates before and after the intervention for cephalosporins and fluoroquinolones, respectively. The choice of these drug groups is based on the European Surveillance of Antimicrobial Consumption (ESAC) quality indicators for the outpatient sector [25] See Fig. 1.

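### The confirmatory model counts antibiotic prescriptions while the primary outcome counts patients with an antibiotic, and the model's offset is not tied to the outcome's denominator

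*Protocol article*

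**What the plan says.** **Outcome.** Trial design says that the overall antibiotic prescription rate is "measured as the proportion of patients with antibiotic prescriptions out of all patients with a prescription". Objectives says the same, and Outcomes repeats it: "measured as the proportion of patients with antibiotic prescriptions out of all patients with prescriptions". Both numerator and denominator are counts of patients.

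**Eligibility score.** The first item of Table 1 (Participants) builds the score on the same ratio: "Overall prescription rate (ratio of patients with antibiotic prescriptions to patients with any prescription". This is an inclusion item and not an outcome definition, but it shows that the patient counts are already produced.

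**Model.** Statistical methods assigns a negative binomial regression to the primary outcome. In it, "the number of antibiotic prescriptions after the intervention(s) is considered as the dependent variable, the number of patients is treated as the offset variable". Study group and regional association are fixed effects, and the pre-intervention rate is a covariate.

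**Status.** The same section reserves confirmatory interpretation for the primary intention-to-treat analysis. It reports incidence rates and rate ratios.

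**The concern.** The numerator changes from patients to prescriptions between the outcome definition and the model, and nothing in the article equates the two. The follow-up period T1 runs for 15 months, so one patient can receive several courses. Repeat or switched courses add to the model's count but leave the defined outcome unchanged.

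The interventions could plausibly act on the two quantities differently. The article also aims to improve the choice of agent, and the training modules cover delayed prescribing and safety netting. Such content may change how many courses a treated patient receives as well as who is treated at all.

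At stake is what the adjusted p values and rate ratios refer to. If the model is run literally, the confirmatory claim concerns prescriptions per patient while the paper's primary outcome is a proportion of patients. If the wording is corrected only after the data are seen, there are two candidate primary results to choose between.

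**Working it through.** **1. Does the sample size section settle the definition?** Inputs (Sample size): 12% in control; 8.7%, 8% and 7% in groups A, B and C; two-sided type 1 error 1.67%; Poisson model; 2000 practices per group, 1250 in C.

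A Wald comparison of two Poisson rates with one unit of exposure per practice gives n = (z_α/2 + z_β)² (r1 + r2) / (r1 − r2)².

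- Control versus A: (2.3933 + 0.8416)² × (0.12 + 0.087) / 0.033² = 10.464 × 190.08 ≈ 1989.1, so 1990 per group (stated: 2000).
- Control versus B: 0.04 / √(0.12/2000 + 0.08/2000) = 4.00; Φ(4.00 − 2.393) = 94.6% (stated: 94.6%).
- Control versus C: 0.05 / √(0.12/2000 + 0.07/1250) = 4.64; Φ(4.64 − 2.393) = 98.8% (stated: 98.8%).

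The stated figures reproduce. The formula takes a rate and does not ask whether patients or prescriptions were counted, so it does not show which quantity was meant.

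**2. How the two ratios relate.** Write p for the proportion of patients with a prescription who receive an antibiotic, m for the mean number of antibiotic prescriptions per patient who receives any, and s for the share of offset patients who have any prescription. Index 0 is control and 1 is intervention.

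- Outcome ratio = p1/p0.
- Modelled ratio = (p1/p0) × (m1/m0) × (s1/s0).

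If the offset means patients with a prescription, s = 1 in both arms and the last factor drops out. The ratios then agree only when m1 = m0.

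**3. Size, with p from the article and m assumed.** The outcome ratio is 8.7/12 = 0.725. Keep the same denominator in both measures (s1/s0 = 1):

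| m, control | m, intervention | Modelled ratio |
|---|---|---|
| 1.3 | 1.3 | 0.725 |
| 1.3 | 1.2 | 0.725 × 1.2/1.3 = 0.669 |
| 1.5 | 1.3 | 0.725 × 1.3/1.5 = 0.628 |
| 1.3 | 1.4 | 0.725 × 1.4/1.3 = 0.781 |

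**4. Why m1 = m0 cannot be taken for granted.** Randomization balances m at baseline, but m in T1 is a mean over patients who are still treated. Take 1000 patients with a prescription and m = 1.3 in control: 120 treated patients and 156 prescriptions. Suppose that all 33 spared patients would have had one course. Then 87 patients and 123 prescriptions remain, m1 = 123/87 = 1.41, and the modelled ratio is 123/156 = 0.788 against an outcome ratio of 0.725. Here the ratios diverge although no remaining patient is treated differently.

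**The case against.** The strongest reply is that the model sentence is shorthand. Statistical methods ties the model to the primary outcome and to a change in prescription rates, and elsewhere the article uses that kind of label for the patient proportion. The baseline covariate is most naturally the defined rate. The article is loose with these terms in other places: items 2 and 3 of Table 1 set patients over prescriptions under the name of a rate, and the secondary models name a rate as dependent variable while also using an offset. A condensed article may have compressed a correct full plan. This is a fair reading and it limits how firmly one can say the wrong quantity will be analysed. It does not remove the conflict, because outcome and model are both spelled out, they differ, and no sentence links them.

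A reader might go further in three ways that the article does not support.

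- **That neither part of the model matches the outcome.** The offset is an undefined patient count. It may well mean patients with a prescription, so a mismatch in the denominator is not established.
- **That the confirmatory result would be reversed.** This is possible in constructed examples, but the article gives no distribution of courses per patient. With equal m the ratios are identical.
- **That patients with any prescription is itself a faulty denominator**, because a spared patient who needs no other drug leaves it. Per 1000 patients, with 33 antibiotic patients avoided, the measured rate would be 87/983.5 = 8.85% if half of them drop out and 87/967 = 9.00% if all do. The ratio is then 0.74 to 0.75 instead of 0.725. The 50–100% is assumed and the shift is small. This is a separate design preference and not an inconsistency in the plan.

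**Conclusion.** The point holds for the numerator: the outcome counts patients with an antibiotic and the confirmatory model, as written, counts prescriptions. For the denominator it holds only in that the offset is unspecified and should be named. This is a contradiction between two stated rules, not detail left to an analysis plan.

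The size cannot be computed from the article. Under assumed means of 1.2 to 1.5 courses per treated patient, a patient-level ratio of 0.725 could appear as anything from 0.628 to 0.781, and it stays at 0.725 when the mean is equal across arms. These figures show how sensitive the result is and do not predict bias. The stated sample size and power reproduce and are unaffected by the disputed wording.

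**What to change.** In Statistical methods, define the primary model as follows:

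- dependent variable: number of patients with at least one antibiotic prescription in T1;
- offset: log of the number of patients with any prescription in T1;
- baseline covariate: the same ratio in T0.

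Prescriptions per patient may be kept as a supportive analysis and labelled as such. A sensitivity analysis with all treated patients as offset is optional and not needed to correct the error.

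The cost is a change of wording in the model definition. The eligibility score already requires both patient counts for T0, and the same data sources supply them for T1, so no new data are needed. The change should be recorded before T1 data are analysed, so that the primary quantity is not chosen with results in view.
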